## Oncogene-driven Targeted Therapy

Current cancer therapeutics are based upon population statistics by disease site and histology and lead to standard protocols prescribed in consecutive lines (i.e., first, second, and third). However, today there are also several models for selecting molecular targeted therapies based upon tumoral molecular abnormalities (i.e., mutations, insertions, deletions, rearrangements, or gene amplifications). Examples of oncogene-driven therapy include:

- EGFR mutation : afatinib, erlotinib, gefitinib;
- BCR-ABL translocation : imatinib;
- KIT mutation: imatinib and sunitinib;
- HER2 amplification: trastuzumab and lapatinib
- B-RAF mutation: vemurafenib;
- ALK rearrangement: crizotinib;
- PI3K and mTOR pathway: everolimus and temsirolimus;
- SMO mutations : vismodegib;
- TP53 mutations: bevacizumab [5];
- Additional examples (<http://www.cancer.gov/cancertopics/factsheet/Therapy/targeted>).

Historically, only 10-40% of tumors had known “oncogenic drivers.” Thus, for the vast majority of tumors, possible genomic alterations were unknown. Therefore, therapeutic decisions were made according to decades-old treatment protocols that are unsatisfactory at the individual patient level, because more than 50% of patients do not respond to standard chemotherapeutic regimens. But, even for tumors with an oncogenic event identified using outdated genomic analyses, the match with selected therapeutics does not predict efficacy or clinical benefit in about half of patients. However, with next generation sequencing and our increasing understanding of cancer genomics, we may be able to improve upon these statistics.

As of October 2013, Foundation Medicine, Inc. provides a CLIA-certified assay called FoundationOne™ that utilizes comprehensive next generation sequencing of routine formalin-fixed paraffin-embedded (FFPE) tissue or blood specimens. The test simultaneously sequences the entire coding sequence of 236 cancer-related genes plus 47 introns from 19 genes often rearranged or altered in cancer. **The average turnaround time for the test to be completed is currently 14-17 days from receipt of the sample.**

The current study will perform tumor molecular profiling through FoundationOne™ to navigate patients to a matched therapy at the discretion of their treating physician. For those patients with an actionable tumor alteration, matched therapy will be recommended by the Study Committee (or Molecular Tumor Board) from either FDA approved drugs or matched agents under investigation in a separate clinical trial. Those patients, for whom there are no available matched treatments, will serve as the unmatched therapy controls.

Patients with no actionable alterations by FoundationOne™ will be considered to have completed their participation in the study. Their basic data will be captured including demographics and tumor type and accounted into the denominator for feasibility analysis.

## Rationale

*Rationale for Group 3: Use of FoundationOne™ panel to match patients with previously treated advanced disease to targeted therapies.* In solid tumors, targeted therapies are often both developed and applied in metastatic malignancies after conventional approaches have failed. In this stage, tumors often have heterogeneous cell populations and their biology is increasingly complex. Therefore, it is crucial to have comprehensive molecular testing in order to identify the underlying multiple alterations in each tumor. As in CML, detecting and targeting a single alteration may induce responses and increase survival. However, it is unlikely to result in dramatic improvements because single gene testing is not adequate to predict the behavior of these complex tumors and the majority of cases approached with “hot spot” testing will not identify a driver alteration. In line with this, we have previously performed and published on the use of molecular testing in this context. Our Phase I trial of targeted agents was designated PREDICT, and we were able to demonstrate higher than expected response rates in the advanced, refractory metastatic setting even with a panel of 12 genes.[6] In fact, response rates were 27% in patients with heavily pretreated metastatic disease and one mutation that were administered a targeted therapy that was matched for their mutation (as compared to 5% when they were not matched). Moreover, the survival was 4 months longer in the matched group versus the unmatched group (non-randomized trial;  $P < 0.05$ ). Progression-free survival was also longer in the phase I matched treatment setting, as compared to the patients’ own previous conventional therapy ( $P < 0.05$ ). This trial therefore showed modest, but real, improvements, and formed a proof-of-principle for molecular matching and matched therapy.

However, as mentioned, the original PREDICT trial was limited by the molecular assays available at that time—12 single gene assays. Inevitably, small amounts of biopsy material meant that most patients could have only 3-5 of the 12 tests analyzed; furthermore, performing single gene tests was labor intensive, time consuming, and expensive. Most importantly, such a panel of only 12 genes is now known to represent only a minute fraction of the genes involved in tumor maintenance and progression. When more comprehensive molecular assays are exploited, patients with metastatic disease are often found to have multiple genomic alterations in their tumors rather than the single alteration or no alteration generally detected with far less comprehensive surveys of the cancer genome. With the current comprehensive FoundationOne™ molecular test, prospective evaluations of its utility are crucial for individualizing the administration of targeted agents in incurable neoplasms. In summary, as compared to earlier studies, the current study will have increased sequencing capabilities, increased knowledge of actionable genomic alterations, and increased access to drugs to target these genomic alterations, making Group 3 an essential part of the trial.

*Rationale for Group 1 and Group 2: Use of FoundationOne™ genomic profiling to match treatment naïve patients with targeted therapies.* It may also prove important to utilize molecular testing earlier in the course of the disease, when tumors are less complex, and targeting their alteration(s) could conceivably have a transformational impact. As mentioned above, moving imatinib therapy from late-stage CML to newly diagnosed disease revolutionized outcomes for this type of leukemia. Instead of inevitable death in half of patients at 4 years after diagnosis, patients now have a near-normal life expectancy. In solid tumors, matched targeted therapy has not yet been applied in newly diagnosed disease despite the fact that treatment naïve solid cancers are much less heterogeneous earlier than later in their disease natural history. Furthermore, as a general principle, strategies/therapies that show proof-of-principle efficacy in late-stage malignancies can be expected to demonstrate significantly higher response rates and survival impact in early disease.

Designing such a trial is complicated because one must take into consideration conventional therapies. **However, the I-SPY trial in breast cancer has already set the precedent for introducing novel, and even experimental drugs, into patients with newly-diagnosed, high-risk breast cancer. In that trial, MammaPrint is used to define high-risk; a high-risk test result means that the cancer has a 29% risk of relapsing within 10 years without any additional treatments after surgery.** However, I-SPY uses Bayesian statistics to allocate patients to treatment. As a result, a patient with a BRCA mutation may or may not receive a PARP inhibitor despite our knowledge that these work in this patient population. With the I-PREDICT trial, we propose the use of molecular profiling (FoundationOne™ assay) and matching patients to drugs based on the target(s) that exist in their tumor. For this trial, we will employ a more conservative definition of high-risk than was used in I-SPY. That is, patients who have a 50% or higher risk of death within two years (as estimated by their physician and according to 2014 NCDB data in Figure 1), or patients that already have locally advanced or metastatic disease at the time of initial diagnosis. Thus, the I-PREDICT clinical trial employs an innovative method to estimate potential efficacy of therapeutics in order to guide the choice of therapies for each individual patient in the early or late phases of disease. This trial addresses unmet needs.

We hypothesize the following:

- Obtaining treatment with targeted therapy after the treating physician receives recommendations based upon actionable genomic alteration(s) will be feasible for treatment naïve patients.
- Patients who receive targeted therapy based upon recommendations from actionable genomic alteration(s) will yield anti-tumor activity.
- Eight-week regression rates will be higher in treatment naïve patients than in previously treated patients.
- Overall survival in treatment naïve patients will be greater than expected according to historical controls matched for stage and other known prognostic factors.
- In previously treated patients, the progression-free survival on matched therapy will be greater than on their last unmatched therapy.
- Patients who receive targeted therapy based upon recommendations from actionable genomic alteration(s) will demonstrate conversion of unresectable to resectable disease.

I-PREDICT may provide feasibility and response information that will be fundamental for designing definitive randomized trials that may change the paradigm of cancer therapy. Eventually, if clinically validated, the data would enable physicians and molecular biologists to select the optimal drug (or drug combination) for each patient based upon their personal tumor genomics. The new approach aims to address the prediction of efficacy of chemotherapeutics or targeted agents (approved or in clinical trial) at an individual level. We will look for known alterations by next generation sequencing at Foundation Medicine (DNA based). If there is a known oncogenic event, the matched targeted therapy will be recommended.

## **Study Objectives**

Below is a detailed description of Primary and Secondary objectives of the study.

### **Primary Objectives**

To determine the feasibility of using molecular testing to determine targeted therapy for patients with newly diagnosed (Groups 1 and 2) and previously treated (Group 3) cancers with incurable biology ( $\geq 50\%$  2-year cancer-associated mortality as estimated by two oncologists and where appropriate according to 2014 NCDB data in Figure 1) after their treating physician receives recommendations based upon genomic analysis for molecular alterations.

### **Secondary Objectives:**

Assess the:

1. Ability to enroll patients in Groups 1, 2 and 3
2. Turnaround time for genomic analysis
3. Ability to identify actionable genomic alterations
4. Ability of treating physicians to wait for molecular information in order to start treatment
5. Ability to obtain insurance coverage in order for patients to receive molecularly targeted matched treatment based on genomic analysis

### **Exploratory Objectives:**

Assess the:

1. Activity of molecularly targeted matched treatment and physician's choice of traditional systemic chemotherapy treatment
2. Incidence of serious adverse events in molecularly targeted matched treatment and physician's choice of traditional systemic chemotherapy treatment

### **Endpoints**

#### **Primary Endpoint:**

The proportion of patients who receive molecularly targeted matched treatment **after recommendations** based on genomic analysis

#### **Secondary Endpoints:**

Determine the:

1. Proportion of patients that consent of all patients approached for the study
2. Time from informed consent to the receipt of FoundationOne™ genomic analysis
3. Proportion of patients with actionable genomic alteration
4. Proportion with insurance coverage for receiving molecularly targeted matched treatment based on genomic analysis

#### **Exploratory Endpoints**

Estimate the:

1. Overall response rate (ORR) defined as partial (PR) or complete response (CR) occurring at any point during treatment according to Response Criteria in Solid Tumors (RECIST) 1.1 in all treatment groups
2. Regression rate as a percent defined by best percent size reduction in target lesions from baseline to discontinuation in all groups
3. Progression free survival (PFS) defined as time from first dose to disease progression or death, whichever occurs first
4. Overall survival (OS) defined as time from first dose to death due to any cause
5. Resection rate as a percent of patients previously considered unresectable that are able to be resected in all groups
6. Change in biochemical tumor markers of disease as defined as the best percent change from baseline in relevant tumor markers from first dose to discontinuation
7. Incidence of serious adverse events in all groups according to CTCAE v4.03

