| Duration of administration            | 
Arm A
 
 
• Groups 1 and 2 = <math>\sim 8</math> week cycles of a regimen of <math>\geq 1</math> drug that targets molecular alteration(s) followed by disease appropriate imaging (i.e., PET-CT vs. CT vs. MR imaging) followed by crossover to treating physician's choice of systemic chemotherapy for SD or PD per RECIST, or unacceptable toxicity but to remain on I-PREDICT recommended regimen if CR, PR by RECIST 1.1
 
• Group 3 = <math>\sim 8</math> week cycles of a regimen of <math>\geq 1</math> drug that targets molecular alteration(s) followed by disease appropriate imaging (i.e., PET-CT vs. CT vs. MR imaging) with cessation of therapy if PD or unacceptable toxicity
 
 
Arm B
                                                                                                                                                                                                                                                                                                                                                                                                                                                                                                                                |

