### **Study Group 1 and Group 2 (treatment naïve)**

ARM A:

A matched treatment regimen will be administered for approximately 8 weeks as dictated by recommendations for approved anti-cancer agents or as dictated by clinical trials. Disease-appropriate imaging (i.e., PET-CT vs. CT vs. MR imaging) will be performed at approximately week 8 according to standard of care or required clinical trial practices. Objective tumor response will be determined according to RECIST v1.1 and this First Response assessment will guide subsequent treatment according to the following:

3. Patients demonstrating a PR or CR per RECIST 1.1 will continue treatment until
  - a complete response persists for at least six months
  - the tumor becomes resectable
  - their tumor response declines to SD or PD
  - they experience unacceptable toxicity.

4. Patients demonstrating SD or PD per RECIST 1.1 will be removed from matched therapy and placed onto the treating physician's choice of systemic chemotherapy appropriate to their disease. Alternatively, the treating physician may continue matched therapy at their discretion if there are no effective traditional systemic chemotherapy regimens available.

Patients who experience SD but short of PR while on matched treatment may, after experiencing progressive disease while receiving treating physician's choice of systemic chemotherapy appropriate to their disease, return to their prior matched treatment and will be monitored again for benefit. The degree of objective tumor response observed at the patient's First Response Assessment on the original matched treatment, will then guide subsequent treatment according to the following:

1. Patients demonstrating a 10-29% decrease in the sum of diameters of target lesions (First Response Assessment) will resume treatment with the original matched treatment regimen. Treatment will continue until:
  - a complete response persists for at least 6 months,
  - their tumor becomes resectable,
  - they experience progressive disease (PD), or
  - they experience unacceptable toxicity.
2. Patients demonstrating a <10% decrease in the sum of diameters of target lesions (First Response Assessment) will then receive the traditional second-line standard of care treatment appropriate for their disease.

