### **Best Overall Response**

Best response is the maximal response recorded from the start of a treatment until the end of treatment taking into account any requirement for confirmation.

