## **6.4 Sample Size Calculation**

All exploratory analysis will test the hypothesis of greater response rate in Arm A than that in Arm B. With an estimated sample size of 30 (ARM A) and 45 (ARM B) in each group, we can estimate the response rate with a standard error no larger than 0.09 and 0.07, respectively. We will have sufficient statistical power to detect the difference between groups only if the difference between groups is sufficiently large. For example, with the sample size of 30 and 45 for Arm A and Arm B, we will have 79% power to detect the response rate of 0.25 and 0.05 between the two arms with one-sided 10% type I error rate using the continuity corrected chi-square test.

We will have more than 80% power to detect the difference between Arm A and Arm B using the log-rank test when the median PFS is 4 months and 2 months for the two arms, respectively.

In addition, in Group 1A, we will estimate the proportion of patients who are initially unresectable (as deemed by two surgeons) but converted to resectable (as deemed by two surgeons) after 8 weeks of the matched treatment, or if ever resected. With 30 patients, we expect to see at least one patient becomes resectable with a probability of 0.79, 0.96, and 0.99 if the conversion rate is 0.05, 0.10, and 0.15, respectively. We expect to see at least 2 patients become resectable with a probability of 0.82 and 0.95 if the conversion rate is 0.10 and 0.15, respectively. One-sided nominal level at 10% will be used to declare statistical significance. No P value adjustment for multiplicity will be applied due to the exploratory nature of the study. All study results need to be confirmed by future studies with larger sample sizes.

- The response rate (proportion of patients reaches CR or PR) will be estimated based on RECIST for each patient group and each treatment arm.
- The tumor regression rate (in %) will be calculated by the percent tumor size reduction from baseline to after treatment will be determined in and across patient groups.
- Progression-free survival (PFS) and overall survival (OS) will be determined in and across patient groups and treatment arms.

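### Best response and best regression run over time on treatment, but the protocol sets that time differently by arm and group, so the exploratory comparisons use unequal windows and regression has three definitions.

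*Protocol*

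**What the plan says.** **Endpoint windows.** Section 1.5 counts an objective response "occurring at any point during treatment according to Response Criteria in Solid Tumors (RECIST) 1.1 in all treatment groups" and defines regression as "Regression rate as a percent defined by best percent size reduction in target lesions from baseline to discontinuation in all groups". The Study Summary repeats both. Section 5.2 adds: "Best response is the maximal response recorded from the start of a treatment until the end of treatment". All three windows last as long as treatment lasts.

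**Time on treatment.**
- Groups 1 and 2, Arm A: the Study Summary has an 8-week course and imaging "followed by crossover to treating physician's choice of systemic chemotherapy for SD or PD per RECIST, or unacceptable toxicity". Section 3.2 agrees: "Patients demonstrating SD or PD per RECIST 1.1 will be removed from matched therapy and placed onto the treating physician's choice of systemic chemotherapy". It adds two exceptions. The physician may continue matched therapy when no effective chemotherapy exists. A patient whose first scan showed a 10-29% decrease resumes the matched regimen after progressing on chemotherapy.
- Group 3, Arm A: the Study Summary describes 8-week cycles "with cessation of therapy if PD or unacceptable toxicity".
- Arm B, all groups: the Study Summary continues until progression, unacceptable toxicity, six months of complete response, or resectability.
- Section 4.2 has tumour assessments about every 8 weeks.

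**Comparisons.** Sections 6.4 and 6.6 test for a higher response rate in Arm A than in Arm B, at a one-sided 10% level. The Study Summary asks whether regression is higher in Groups 1 and 2 than in Group 3. The hypothesis in Section 1.3 is narrower: "Eight-week regression rates will be higher in treatment naïve patients than in previously treated patients". Sections 6.4 and 6.6 use a further definition: "The tumor regression rate (in %) will be calculated by the percent tumor size reduction from baseline to after treatment".

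**The concern.** A best value over a long course and a best value over a short one are different quantities. A patient with stable disease in 1A or 2A normally has one scan on the initial matched course. A similar patient in Arm B or 3A, under the Study Summary, stays on the regimen and can still reach a partial response there. Two stated questions depend on this contrast: Arm A against Arm B within Groups 1 and 2, and treatment-naïve against previously treated patients.

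The word treatment can also be read to include chemotherapy given after crossover. Its shrinkage would then be credited to Arm A. Resection has the same ambiguity, because Group 1A counts patients converted after 8 weeks of matched treatment or ever resected, and Section 6.6 compares 1A with 1B.

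Finally, Section 1.3 states an eight-week hypothesis that neither Section 1.5 nor Sections 6.4 and 6.6 measure. The results are meant to inform confirmatory trials, so a shortfall in Arm A that came only from the window could mislead their design.

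**Working it through.** **1. The plan's power figure.** Inputs from Section 6.4: 30 and 45 patients, response rates 0.25 and 0.05, one-sided 10%, continuity-corrected chi-square.
- Pooled rate = (30×0.25 + 45×0.05)/75 = 0.13
- Null SE = √[0.13×0.87×(1/30+1/45)] = 0.0793
- Alternative SE = √[0.25×0.75/30 + 0.05×0.95/45] = 0.0855
- Correction = 0.5×(1/30+1/45) = 0.0278
- Power = Φ[(0.20 − 0.0278 − 1.2816×0.0793)/0.0855] = Φ(0.826) = 79.6%

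The stated 79% reproduces.

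**2. Effect of a short Arm A window on power.** Let f be the share of Arm A responses that would first appear after week 8. The documents give no value, so f is assumed. Take 0.25 and 0.05 as any-time rates, leave Arm B at 0.05, and ignore the two exceptions. The observable Arm A rate is 0.25×(1 − f).

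| f | Arm A rate | Power |
|---|---|---|
| 0 | 0.250 | 79.6% |
| 0.1 | 0.225 | 72% |
| 0.2 | 0.200 | 64% |
| 0.3 | 0.175 | 53% |
| 0.4 | 0.150 | 42% |
| 0.5 | 0.125 | 31% |

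**3. Same tumours, two stopping rules.** This is a simulation of 400,000 patients per setting. Assumptions: first-scan change has mean −5% and SD 25; each later 8-week step has SD 10 and mean growth of 0, 3 or 6 points; measurement SD is near 0, 5 or 8; there are at most six scans. Response is a decrease of at least 30%; progression is a rise of 20% over nadir. Under the short rule only responders continue past the first scan. Under the long rule treatment runs to progression. The two exceptions are not modelled. The extremes of measurement error are:

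| Growth | Measurement SD | ORR short / long | Gap (points) | Mean best change short / long |
|---|---|---|---|---|
| 0 | near 0 | 15.9% / 32.2% | 16.3 | −6.8% / −15.3% |
| 0 | 8 | 17.0% / 35.2% | 18.2 | −6.5% / −16.3% |
| 3 | near 0 | 15.9% / 24.4% | 8.5 | −5.9% / −10.4% |
| 3 | 8 | 17.1% / 28.1% | 11.0 | −6.0% / −12.1% |
| 6 | near 0 | 15.9% / 19.9% | 4.0 | −5.5% / −7.7% |
| 6 | 8 | 17.1% / 23.5% | 6.4 | −5.6% / −9.4% |

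The response gap is about 4 to 18 points and the regression gap about 2 to 10 points, with no true difference. Most of the gap remains when measurement error is near zero, so it comes mainly from further real shrinkage during longer treatment. A second model (log change per 8 weeks with mean 0.05 and SD 0.25, 5% noise, up to six scans) gave 5.5% against 12% to 23%, a gap of about 6 to 17 points.

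**4. Which comparisons are affected.** On the per-regimen reading, 1A and 2A have the shorter window against 1B and 2B, and against Group 3. If arms are pooled within the naïve groups, only the Arm A share carries the effect, which is 30/75 = 40% on the planned split. Under the Study Summary, 3A and 3B both continue past stable disease, so that contrast is not affected in the same way.

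**The case against.** **The route back.** A reader might infer that a late response on matched therapy can never be seen in 1A or 2A. Section 3.2 does not support that. Patients with a 10-29% first decrease can resume the matched regimen and are monitored again. In the second model with upward drift, about 92% to 100% of late responders had shrunk by at least 10% at week 8, so this route would reach most of them. Discretionary continuation may also be common, since the eligibility criteria admit patients without effective conventional options. This stands in part: treatment resumed after progression on chemotherapy is not the same as uninterrupted treatment.

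**The mechanism.** A reader might blame the number of scans. The near-zero-error results show that longer treatment is the main cause. Best response over the treatment period is also ordinary RECIST practice, and is sound as a within-arm description.

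**Continuation past stable disease.** It might be taken as settled that Arm B and Group 3 are followed to progression. That rests on the Study Summary. Section 3.2 gives Arm B only a course and scan at about 8 weeks. It gives 3A no rule for stable disease at the first scan, and stops 3A responders when they decline to stable or progressive disease. The true imbalance is therefore uncertain.

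**The crossover reading.** Section 5.2 speaks of the start of a treatment, which favours a window per regimen. The resection plan already asks for an 8-week result alongside the ever-resected one. Both points weaken the crossover reading, but nothing in the protocol excludes it.

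**Consequence.** The endpoints are exploratory, the study is non-randomised and hypothesis-generating, and confirmation is required. On the per-regimen reading the distortion makes a false claim for either hypothesis less likely. These points limit the severity.

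**Conclusion.** The point holds at moderate severity. The protocol ties response and best regression to time on treatment and then sets that time differently for 1A/2A than for 1B/2B and, per the Study Summary, Group 3. It also hypothesises an eight-week regression that its endpoint and analysis sections define in two other ways. On the per-regimen reading the direction is against both hypotheses, so a null result could be partly an artefact. On the crossover reading, chemotherapy effect is added to Arm A.

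The size cannot be derived from the documents. The 4 to 18 points, and the fall in power to 64% or 42%, rest on assumed tumour kinetics and assumed late-response shares, and neither allows for the two exceptions. A reader might infer an artefact close to the 20-point planning contrast (0.25 against 0.05). That is only the top of an assumed range. The primary feasibility endpoint is not affected.

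**What to change.** In the Study Summary, Section 1.5, and Sections 6.4 and 6.6:
- Use change from baseline to the assessment at about week 8 for the naïve-versus-Group 3 regression comparison, as Section 1.3 hypothesises. Use response at that assessment for Arm A versus Arm B in Groups 1 and 2. Section 3.2 schedules this scan in every arm and group.
- Keep best response and best regression to discontinuation as within-arm description.
- Tabulate tumour changes and resections after crossover, and those on resumed matched therapy, separately from the initial matched course.
- State that the 79% power applies only if 0.25 and 0.05 are week-8 rates.

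The Study Summary and Section 3.2 must also be reconciled on continuation after stable disease for Group 3 Arm A and for Arm B. Which treatment rule applies is for the investigators to decide.

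The cost is wording only: no new scans and no change to treatment. The downside is that late responses leave the formal comparison and appear only descriptively.
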